### Study objectives

#### ***Aims***

1. To examine the effectiveness of the service up to 12-months post-intake in improving a range of health outcomes (including length of stay in hospital, number of admissions, health state, preference based health state, and health-related costs).

2. To examine the effect of a range of factors including comorbidities, sociodemographic factors, and type of intervention received, on the health state, preference-based health state, length of stay in hospital, number of admissions, and health-related costs of people attending the service up to 12-months post intake.

3. To determine the difference in health between clients attending the service before and after receiving intervention and the general population using Australian population normative data.

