#### ***Hypotheses***

1. Health will be maintained or improve over time from intake (baseline) to 12-months after intake with a small average effect size anticipated for improvement (effect size ≤ 0.2).

2. Health outcomes will be moderately to strongly and negatively associated with the number of chronic diseases (effect size ≥ 0.5).

3. Days in hospital and inpatient admission costs will decrease after intake to the service compared with before intake to the service.

4. The health of clients attending the service will be worse than the general population using Australian population normative data at all times (effect size ≥ 0.2).

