### Study measures

All study measures will be completed at the site of the interdisciplinary service at baseline. However, people who are unable to attend the clinic for a follow-up assessment will be posted self-report questionnaires. Questionnaires will be self-administered except in cases where it is clear that the patient is unable to complete the questionnaire due to an impairment (such as visual disturbance) that makes self-completion difficult. In these cases questionnaires will be interviewer-administered. Table 1 provides a summary of each of the measures at each time point.

**Table 1 T1:** Study outcome measures at each follow-up time

**Baseline**	**3 months**	**6 months**	**12 months**
SF-36	SF-36	SF-36	SF-36
BMI and waist measurement	BMI and waist measurement	BMI and waist measurement	BMI and waist measurement
Comorbiditymeasure	Comorbidity measure	Comorbidity measure	Comorbidity measure
K6			
Medical Outcomes Study Social Support Survey			
TUG	TUG	TUG	TUG
Self-reported health perception question	Self-reported health perception question	Self-reported health perception question	Self-reported health perception question
Sociodemographic information			
	Intervention data	Intervention data	Intervention data

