### Disease burden and number and type of comorbid conditions

Disease burden and the number and type of comorbid conditions will be measured using a self-report comorbidity measure [21]. Using the comorbidity measure [21] 25 common chronic diseases (excluding depression) are rated for the degree to which each condition interferes with daily activities. Scores on this measure have been found to correlate more strongly with health state measured using the SF-36 than other comorbidity indices in community samples [22,23].

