### Data analysis

Descriptive statistics and exploratory plots (boxplots or histograms) will be used to describe the outcome variables (e.g., health state, preference based measure of health, hospital utilisation, and costs) and potential predictors (e.g., age, employment status).

SF-36 scale raw scores will be transformed to a 0 to 100 scale. Results will be analysed using the 8 scales and the summary scores where appropriate. Scatterplots of the relationship between variables will be examined to check for linearity or potentially non-linear associations. Mean SF-36 scores will be plotted over time by demographic and disease subgroups to visually examine chronic disease progression. Regression models will be used to examine the effect of time and predictors on post-intake SF-36 scores. The scores will be modelled at 3- to 12-months with the baseline score as a predictor in order to: i) analyse the change from baseline; ii) help control for regression to the mean [36]. Mixed models will be used with subject-specific intercepts to model the dependence in results over time from the same subject. The lasso technique will be used to choose the best set of predictor variables from an initially large set of potentially important variables [37]. The residual distribution of the best model will be examined to check that it is approximately normally distributed with no large outliers. The count outcome variables (i.e., cost, days in hospital, and number of hospitalisations) will be analysed using the model described above but assuming a Poisson distribution.

The predictors to be examined in all of the models will be: BMI and waist measurement, disease burden, number and type of comorbidities, self-reported health perception, age, gender, indigenous status, country of birth, language (other than English), marital status, home ownership, highest level of education, occupation and employment status, length and type of intervention; and baseline psychological distress or wellbeing, functional and structural social support, and physical function. Health (measured using the SF-36) and the preference based measure of health will be examined as predictors for count outcomes.

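### Hypothesis 2 concerns how disease count relates to health, but the only inferential predictor model adjusts for baseline SF-36 and lets the lasso drop the count

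*Protocol article*

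**What the plan says.** The Hypotheses section of the protocol article states: "Health outcomes will be moderately to strongly and negatively associated with the number of chronic diseases (effect size ≥ 0.5". It does not say whether 0.5 is a correlation, a standardised mean difference or something else. Aim 2 is broader: "To examine the effect of a range of factors including comorbidities, sociodemographic factors, and type of intervention received, on the health state".

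The Data analysis section names the tool for predictors: "Regression models will be used to examine the effect of time and predictors on post-intake SF-36 scores". It then fixes the conditioning: "The scores will be modelled at 3- to 12-months with the baseline score as a predictor in order to: i) analyse the change from baseline". Control of regression to the mean is given as the second reason. Mixed models with subject-specific intercepts handle the repeated visits. Selection follows: "The lasso technique will be used to choose the best set of predictor variables from an initially large set of potentially important variables". The candidate list, which applies to every model, begins "BMI and waist measurement, disease burden, number and type of comorbidities, self-reported health perception, age, gender, indigenous status".

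The measures section shows that two of these candidates share a source: "Disease burden and the number and type of comorbid conditions will be measured using a self-report comorbidity measure". It adds that scores on this instrument track the SF-36 more closely than other comorbidity indices do.

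The only other analyses of SF-36 described are scatterplots, plots of mean scores over time by demographic and disease subgroup, and t-tests against population norms. None of these is an inferential analysis of disease count.

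**The concern.** Diseases present at intake have already lowered SF-36 at intake. Once baseline SF-36 is in the model, the coefficient for disease count no longer says how much worse health is in people with more diseases. It says how much worse they do afterwards than others who started at the same score. That is a legitimate question, but it is not the one in Hypothesis 2.

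Selection adds a second difficulty. The lasso chooses for prediction and has no reason to protect the variable a hypothesis names. Here the count competes with a burden score from the same questionnaire and with a single-item health rating close in content to the SF-36 general health perceptions scale. A real association of the hypothesised size could come out small, or not be selected, and be read as evidence against Hypothesis 2.

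**Working it through.** **The plan's own figure.** The article gives no calculation for Hypothesis 2. Its minimum of 130 participants is for a 5-point change in social functioning (80% power, two-sided 5%). No SD is given, so 130 cannot be reproduced. It would require an SD of change of about √(130 × 25 / 7.849) = 20.3. Nothing below depends on that calculation; 130 serves only as the sample size in step 3.

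**Inputs.** From the article: the 0.5, the baseline conditioning, the candidate list and n = 130. Assumed, because the article gives no correlations: SF-36 retest correlation 0.6 to 0.8; count correlated equally (r) with baseline and follow-up SF-36; count–burden correlation 0.7 to 0.85. The 0.5 is read in two ways: as r = -0.50, or as Cohen's d, for which r = 0.5/√(0.5² + 4) = 0.24 in size (equal groups).

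**Step 1: baseline SF-36 only.** The standardised coefficient of the count is

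β = (r_YC − r_YB × r_BC) / (1 − r_BC²),

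where Y is follow-up SF-36, B baseline SF-36 and C the count. With r_YC = r_BC = r this is r(1 − r_YB)/(1 − r²). For r = -0.50 and retest 0.67: (-0.50 + 0.67 × 0.50)/0.75 = -0.22.

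| Unadjusted r | Retest 0.6 | 0.67 | 0.7 | 0.8 |
|---|---|---|---|---|
| -0.50 | -0.267 | -0.220 | -0.200 | -0.133 |
| size lost | 47% | 56% | 60% | 73% |
| -0.24 | -0.102 | -0.084 | -0.076 | -0.051 |
| size lost | 58% | 65% | 68% | 79% |

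The equal-correlation assumption matters. If the count also predicts decline, say r_BC = -0.40 and r_YC = -0.50 with retest 0.7, then β = (-0.50 + 0.28)/(1 − 0.16) = -0.26 instead of -0.20. The attenuation is smaller but still about half.

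**Step 2: if burden and self-reported health are also retained.** This takes the burden–SF-36 correlation as 1.15 times that of the count, and self-reported health correlated -0.5 with follow-up and -0.55 with baseline SF-36. The count coefficient is then -0.01 to -0.11 for r = -0.50 and -0.004 to -0.03 for r = -0.24. This is a limiting case, because the plan does not force either variable in.

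**Step 3: lasso selection.** Simulation with n = 130, one follow-up, four correlated predictors (baseline SF-36, count, burden, self-reported health) plus 16 noise predictors, count–burden correlation 0.8, retest 0.6 or 0.7, five-fold cross-validation and 100 runs per setting. All predictors, including baseline SF-36, were penalised.

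| Unadjusted r | Count kept, minimum CV error | Count kept, one-SE rule |
|---|---|---|
| -0.50 | 50–63% | 25–45% |
| -0.24 | 23–40% | 4–13% |

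With 100 runs the simulation error is up to √(0.5 × 0.5/100) = 5 percentage points. A separate run under somewhat different assumed correlations gave 37–52% and 7–33%. The count is often dropped, but not always.

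**The case against.** The article never assigns Hypothesis 2 to this model, and a condensed article may leave a hypothesis-by-hypothesis map to a fuller plan. Baseline adjustment and the lasso are both sound for their stated uses. For learning which factors future studies of change should control for, predictors that add to baseline health are a sensible answer. The study calls its evidence preliminary. Every correlation above is assumed, and the simulation uses one follow-up where the plan has three in a mixed model.

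Most of this stands, and it limits the wording. It does not remove the mismatch: the article says what its predictor model estimates, and that differs from what Hypothesis 2 asserts.

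Three stronger readings are tempting but unsupported.

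- A reader might infer that burden and self-reported health are fixed terms, so the association is bound to vanish. Only baseline SF-36 is stated as a model term. The other two are candidates like the count, and the lasso may drop them and keep it.
- Because "people who are unable to attend the clinic for a follow-up assessment will be posted self-report questionnaires", a reader might infer that postal responders lack measured BMI and waist and so fall out of the SF-36 models. That requires follow-up BMI and waist to be used as covariates, retained by the lasso, and handled by deleting incomplete rows. The article states none of these.
- A reader might conclude that self-reported health must leave the lasso model. Its use as a predictor is defensible, and the article justifies the item by its relation to current, changing and future health. Excluding it is a preference, except in the model that tests Hypothesis 2.

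**Conclusion.** The concern holds in limited form. The only inferential predictor analysis described estimates an association with later SF-36 given baseline SF-36, whereas Hypothesis 2 is about the association with health itself. With retest correlations of 0.6 to 0.8 and equal correlation of the count with baseline and follow-up, baseline adjustment alone removes 47% to 79% of the standardised association, roughly half to three quarters. Lasso selection may weaken or remove it further; how often depends on correlations the article does not give. So a true association of the hypothesised size may, not must, be reported as weak or unselected. The undefined metric of the 0.5 adds to the problem, since the result could not be set against it without a choice made afterwards. It is worth settling before analysis. It does not call the change-over-time analysis into question.

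**What to change.** Test Hypothesis 2 in one separate, pre-specified regression of SF-36 on the baseline number of chronic diseases. Use SF-36 at baseline, or at each time point without baseline SF-36 as a covariate, and name the choice in advance. Keep the count unpenalised. Adjust for age, gender and the socioeconomic indicators, but not for disease burden or self-reported health. State the metric of the 0.5 effect size and report the estimate with its confidence interval on that metric.

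Keep the baseline-adjusted lasso model for change and exploratory prediction, with baseline SF-36 and time unpenalised. State that predictors measured again at follow-up (BMI, waist, the comorbidity measure) enter at their baseline values. The Data analysis section attaches the word baseline only to distress, social support and physical function, so the timing of the others is open.

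The cost is one extra regression and a few sentences. No new data are needed.

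### Length and type of intervention are candidate predictors in the SF-36 models that examine time for Aim 1, so what the time effect means depends on lasso selection and on an unstated coding

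*Protocol article*

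**What the plan says.** Aim 1 of the protocol article is "To examine the effectiveness of the service up to 12-months post-intake in improving a range of health outcomes", and the first hypothesis is that "Health will be maintained or improve over time from intake (baseline) to 12-months after intake".

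The Data analysis section gives the SF-36 analysis for this: "Regression models will be used to examine the effect of time and predictors on post-intake SF-36 scores". It adds that "The scores will be modelled at 3- to 12-months with the baseline score as a predictor", and names analysis of change from baseline as one purpose of doing so. Subject-specific intercepts handle the repeated visits.

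The list of covariates opens with "The predictors to be examined in all of the models will be" and includes "occupation and employment status, length and type of intervention; and baseline psychological distress or wellbeing". No model is exempted. Selection is by lasso: "The lasso technique will be used to choose the best set of predictor variables from an initially large set of potentially important variables".

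In Table 1 (Study measures) the row "Intervention data" is filled at 3, 6 and 12 months and empty at baseline. The section on sociodemographic and intervention data says that length and type of intervention received are recorded. It does not say whether length is a running total, the amount since the last visit, or one total per person.

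**The concern.** Length of intervention is the exposure. It arises after intake and lies between attending the service and the later SF-36 score. The word baseline in the predictor list is attached to distress, social support and physical function. Length has no intake value that could be used instead.

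Aim 1 asks how health changes in people who attend the service and receive whatever care they receive. A time coefficient from a model that also contains treatment received up to that visit answers a different question: how scores change between visits if the amount of treatment stays the same. If the service offsets a background decline, the first quantity can be zero while the second is negative. A reader who takes the time coefficient as the answer to Aim 1 would then report decline in a cohort that was maintained.

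Because the lasso decides whether length stays in, the quantity being estimated could also change with the data.

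**Working it through.** **Plan's own figure.** No figure in the article bears on this time effect. The nearest is the minimum of 130 participants for a 5-point change (80% power, two-sided 5%). No SD is given. Solving back, SD of change = 5 x sqrt(130) / (1.960 + 0.842) = 20.3. The point does not depend on this; 130 is used below only as a study size.

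**Step 1: expected values.** Everything here is assumed, as the article gives no rates. Let S(m) be the sessions received by month m, about one per month on average and varying between people. Let scores fall g points per month in the background and rise g points per session, so the cohort is truly flat:

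Y(m) = constant + slope x baseline - g x m + g x S(m)

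- Time effect from 3 to 12 months without S: 9 x (-g + g) = 0.
- Time effect with S held fixed: -9g, which is -2.25, -4.5 and -9.0 for g = 0.25, 0.5 and 1.0.

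**Step 2: simulation by coding of length.** Random-intercept models at 3, 6 and 12 months, adjusted for baseline, with length forced in (20 data sets of 1,000 people per row). Entries are the 3-to-12-month change in points.

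| g | no length | cumulative | per interval | per-person total |
|---|---|---|---|---|
| 0.25 | 0.0 | -2.2 | -1.2 | 0.0 |
| 0.5 | 0.0 | -4.6 | -2.3 | 0.0 |
| 1.0 | 0.0 | -8.8 | -4.6 | 0.0 |

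Cumulative coding moves the whole gain out of the time effect, and per-interval coding about half. A per-person total does not vary between visits, so with complete visits it leaves the time contrast unchanged. It has a different defect: treatment given after month 3 or 6 is used to explain scores already recorded.

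**Step 3: lasso selection.** With 130 people, g = 0.5, cumulative length and 15 noise predictors, length was kept in 80% of 100 runs. The mean 3-to-12-month time effect was -2.7 when kept and -0.1 when dropped; overall 0.80 x -2.66 + 0.20 x -0.12 = -2.15. This was a pooled lasso that also shrank the time term, so it shows the instability and is not a forecast.

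**Step 4: risk of a false reading.** With 130 people, g = 0.5 and cumulative length forced in, a significant decline appeared in 56% of 150 runs, against 3% without length. The assumed components (baseline SD 20 with slope 0.6, person SD 8, residual SD 10, session-rate SD 0.4 per month) give an SD of change of about sqrt(64 + 64 + 100 + 5.8) = 15.3. That is below the 20.3 implied by the plan, so 56% is on the high side.

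**Step 5: a second set of assumptions, by hand.** Let treatment run from intake for D months, with D uniform on 0.5 to 12. Mean length by month t is [(t^2 - 0.25)/2 + t x (12 - t)] / 11.5:

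- t = 3: 31.375 / 11.5 = 2.73
- t = 6: 53.875 / 11.5 = 4.68
- t = 12: 71.875 / 11.5 = 6.25

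Mean length therefore rises by 3.52 months from month 3 to month 12. At 1 point gained per month treated and 0.4 lost per month in the background, the true change is 3.52 - 3.60 = -0.1, and the time effect at fixed length is -3.6. But 1 point per month implies a treatment contribution of 6.25 points by month 12. If that contribution is instead 3 to 5 points, the rate is 3/6.25 = 0.48 to 5/6.25 = 0.80, and the amount moved out of the time effect is 0.48 x 3.52 = 1.7 to 0.80 x 3.52 = 2.8 points.

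**The case against.** The strongest case on the other side has five parts.

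- **Length is only a candidate.** The article speaks of predictors to be examined and leaves the choice to the lasso. A reader might infer that the Aim 1 model always holds length fixed; the text does not say so. This stands, and the point is therefore conditional on retention. It does not remove the point: a real treatment benefit makes length more predictive and so more likely to be kept.
- **The coding is not stated.** A reader might infer from visit-by-visit collection that length accumulates. Table 1 shows only when the data are collected. This stands too: the effect is full, about half or nil according to the coding. A condensed article may leave coding to a fuller document. The scope of the list, all models with no exemption, is what this article does fix.
- **The time term is not the whole of Aim 1.** All modelled scores are after intake, so time contrasts the 3-, 6- and 12-month visits. Change from baseline also involves the intercept, the baseline term and the covariate values chosen. Adjusted means at each visit's own mean length would recover the total change. That is correct, but the article does not specify such means.
- **Other summaries are unaffected.** The t-test appears only as the basis of the sample size, and the plots of mean scores are descriptive. Neither is stated as the estimate for Aim 1.
- **The benefit is relocated, not lost.** The length coefficient in the same model would carry it. This is right: the harm is a change in what the time effect means and a likely misreading of it.

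It is also fair that Aim 2 needs type of intervention as a predictor, and that the article speaks of models in the plural. It does not say that one fit must answer both aims, but it describes no model for Aim 1 without the intervention variables.

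**Conclusion.** The point holds in conditional form. The article allows the Aim 1 time effect to be conditioned on the treatment received, and leaves it to data-driven selection whether that happens. If length is kept and coded as accumulating or per-interval, a maintained cohort can show a decline between 3 and 12 months.

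For an assumed flat cohort with a background decline of 0.5 points per month, the spurious change is about -4.6 (cumulative, forced in), -2.3 (per interval) or 0 (per-person total). At 0.25 and 1.0 points per month, cumulative coding gives -2.2 and -8.8. The direction requires that the service helps and that recorded length rises over visits. The rates, session frequency and variances are assumptions.

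A reader might go further and conclude that the effectiveness answer is biased toward no effect, by more than the 3-point lower end of the important difference cited in the sample-size section. The documents do not support that. The -3.6 figure needs one assumed benefit rate and length forced into the model, while the plan fixes neither the coding nor the retention of length.

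**What to change.** State two SF-36 models.

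- **Aim 1:** visit effects and change from baseline, from a mixed model with the baseline score and intake covariates only. Exclude length and type of intervention from the candidate list. For predictors measured again at follow-up, such as BMI, comorbidity and self-rated health, say that the intake value is used.
- **Aim 2:** a separate model that adds length and type of intervention received up to each visit, with the coding of length stated. Report these as associations and do not read the time effect from this model.

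The cost is one extra model and some wording in the analysis section. No new data are needed.

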Adjustment will made for wave missing data (where a subject misses an entire visit) using inverse probability weighting [38]. This is a two-stage procedure. In the first stage a logistic regression model is used to predict which subjects are more likely to be missing at each follow-up time. This model will include time, demographic factors and comorbidity factors collected at baseline. The probability of each subject being missing at each time is then calculated and inverted to create a weight that can be used in the regression models described above. As an example, if men at 12-months have a 0.5 probability of responding, then the weight for men is 2 so that the results for those men who responded at 12-months are doubled. This will enable a sensitivity analysis with comparison to the complete case analysis to be conducted.

The health of the study sample (using SF-36 scores) will be compared to Australian normative data [39] matched on select sociodemographic variables such as age, gender and select chronic diseases using unpaired t-tests with 95% confidence intervals.

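### The inverse-probability weight for missed visits is defined two ways: the rule inverts the probability of being missing, the worked example the probability of responding

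*Protocol article*

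**What the plan says.** The Data analysis section of the protocol article handles wave non-response "using inverse probability weighting [38]. This is a two-stage procedure". Stage one is described as a missingness model, in which "a logistic regression model is used to predict which subjects are more likely to be missing at each follow-up time"; its predictors are time and baseline demographic and comorbidity factors. The second stage is given as a rule: "The probability of each subject being missing at each time is then calculated and inverted to create a weight". The weight then enters the regression models set out earlier in the section.

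The illustration that follows names the other probability: "if men at 12-months have a 0.5 probability of responding, then the weight for men is 2". Its effect is to scale up the responders, as the rest of that sentence explains: "so that the results for those men who responded at 12-months are doubled". The stated purpose is: "This will enable a sensitivity analysis with comparison to the complete case analysis to be conducted".

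**The concern.** A responder has to stand in for similar people who did not respond. The less likely someone was to respond, the more people each such responder must represent, so the valid weight is 1/P(responding). The written rule gives 1/P(missing), which falls as the chance of being missing rises.

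The rule also follows naturally from the first stage. The logistic model is for being missing, so its fitted value is P(missing). An analyst who takes the two stages in order would invert that value, and nothing tells them to take the complement first. Checking the code against the worked example would not catch this.

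The weighted analysis is there to show whether drop-out distorts the results. With reversed weights, any difference from the complete-case result would point the wrong way and mislead readers about attrition.

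**Working it through.** **Inputs.** From the protocol article, Data analysis: the rule (invert P(missing)), the example (invert P(responding) = 0.5, weight 2), and the application of the weight to responders. The article gives no response rates by subgroup, so all other response probabilities and the outcome gap in steps 3 and 4 are assumptions.

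**1. Reproduce the plan's figure.** Example: 1/P(responding) = 1/0.5 = 2. Rule: 1/P(missing) = 1/(1 − 0.5) = 2. The two agree only where p = 1 − p, that is, at p = 0.5.

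**2. Weights at other response probabilities p.**

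| p | 1/p (example) | 1/(1 − p) (rule) |
|---|---|---|
| 0.5 | 2.00 | 2.00 |
| 0.6 | 1.67 | 2.50 |
| 0.7 | 1.43 | 3.33 |
| 0.8 | 1.25 | 5.00 |
| 0.9 | 1.11 | 10.00 |

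The first set falls as p rises and the second set rises.

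**3. Direction of the effect on a crude mean.** Take two strata of equal size with response probabilities pA > pB. Each stratum's contribution is its response probability times its weight:

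- Complete cases: pA to pB.
- Weight 1/p: 1 to 1, which restores the original balance.
- Weight 1/(1 − p): pA/(1 − pA) to pB/(1 − pB).

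The last ratio equals (pA/pB) × (1 − pB)/(1 − pA). The second factor exceeds 1 whenever pA > pB, so in this setting the literal rule always leaves a larger imbalance than no weighting.

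**4. Size, under assumed values.** Let the strata means be 50 and 40, so the true mean is 45. For response 0.8 and 0.6:

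- Complete cases: (0.8 × 50 + 0.6 × 40)/1.4 = 45.71, bias 0.71.
- Weight 1/p: (50 + 40)/2 = 45.00, bias 0.
- Weight 1/(1 − p): (0.8 × 5 × 50 + 0.6 × 2.5 × 40)/(4 + 1.5) = 260/5.5 = 47.27, bias 2.27.

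The same calculation for other pairs:

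| Response | Complete-case bias | Literal-rule bias | Ratio |
|---|---|---|---|
| 0.8, 0.6 | 0.71 | 2.27 | 3.2 |
| 0.7, 0.3 | 2.00 | 3.45 | 1.7 |
| 0.9, 0.6 | 1.00 | 3.57 | 3.6 |
| 0.9, 0.5 | 1.43 | 4.00 | 2.8 |
| 0.8, 0.4 | 1.67 | 3.57 | 2.1 |

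The absolute biases are proportional to the assumed 10-point gap, so a 5-point gap halves them. The ratios do not depend on the gap.

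**The case against.** A reader might infer that the plan has adopted 1/P(missing) as its method and that its attrition bias will therefore grow. The text does not support that. The method is named and cited as inverse probability weighting, and the sentence directly after the rule speaks of the probability of responding and doubles the men who responded, which is the correct logic. A wording slip is the likeliest explanation, and an analyst who followed the method's name or the example's words would get the right weights. This stands, and it makes the defect a contradiction whose harm depends on literal coding. It does not remove the defect, because the rule is the operative instruction and the example's number fits both definitions.

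A reader might also infer that the weighting is the only protection against missed visits. It is the only explicitly named adjustment. The same section also plans mixed models with subject-specific intercepts and the baseline score as a predictor. These can use participants with some visits missing and offer some protection if data are missing at random given the model's covariates.

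The bias figures are crude means of two invented strata. The planned outcome models draw on many of the same demographic and comorbidity variables as the weight model. Where those variables are retained and the model is correctly specified, weights that depend only on them do not bias its coefficients, and a wrong weight mainly costs precision. This stands as a limit on the size. It does not remove the risk, since the lasso may drop some of these variables and population-average summaries could still shift.

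Finally, the weighting is described as enabling a sensitivity analysis, and the complete-case result is untouched by the weights. That limits the reach of the error, although a sensitivity analysis with reversed weights cannot do its job.

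**Conclusion.** The point holds as an internal contradiction in a stated analysis rule. The rule gives 1/P(missing), the example gives 1/P(responding), and the chosen value of 0.5 hides the difference. Only 1/P(responding) is valid for weighting responders.

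If the rule is coded literally, the order of the weights is reversed, and the comparison with complete cases moves in the wrong direction. That direction is general for crude means of two equal strata with unequal response. The size, about 1.7 to 3.6 times the complete-case bias, rests on the assumed response pairs and on unadjusted means, and covariate adjustment in the planned models could reduce it. The document does not show that the trial's results will be biased by these amounts, or that the wrong weight will in fact be used.

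**What to change.** Replace the rule with wording such as: for each subject at each follow-up, the probability of responding is obtained from the first-stage model as 1 − P(missing), and each responder's weight at that visit is 1/P(responding) = 1/(1 − P(missing)). Change the example to a value away from 0.5: a response probability of 0.8 gives a weight of 1.25.

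A simple check can be added to the code: within a stratum, the responders' weights should sum to about the number of subjects in it. For 100 subjects with response 0.8, the correct weights give 80 × 1.25 = 100, and the literal rule gives 80 × 5 = 400.

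The cost is one sentence and one example. Data collection, sample size and design are unaffected, and any weights already computed can be recalculated from the same first-stage model.
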